### Main study parameter/endpoint

The primary objective of this non-inferiority study is to determine whether ACL repair will result in at least equal effectiveness compared with ACL reconstruction in terms of the self-reported functional outcome measured by the International Knee Documentation Score 2000 subjective knee evaluation score (IKDC Subjective) 1 year postoperative (Table 1) [23–25].

**Table 1 Tab1:** Oversight of the investigations and follow-up moments

	B	OR	6w	3 m	6 m	9 m	1y	2y	5y	10y
X-ray	x	x					x	x	x	x
MRI	x									
IKDC 2000 Subjective	x		x	x	x	x	x	x	x	x
IKDC 2000 Current health	x	x	x	x	x	x	x	x	x	x
IKDC 2000 History	x	x	x	x	x	x	x	x	x	x
IKDC 2000 Demographic form	x	x	x	x	x	x	x	x	x	x
IKDC Physical examination	x		x	x	x	x	x	x	x	x
KOOS	x		x	x	x	x	x	x	x	x
Tegner score	x		x	x	x	x	x	x	x	x
VAS satisfaction	x		x	x	x	x	x	x	x	x
AP laxity	x		x	x	x	x	x	x	x	x
LSI power tests	x				x	x	x	x	x	x
LSI jump tests					x	x	x	x	x	x
Sport specific fatigue test							x			
Concomitant injury		x								
Rupture pattern		x								
Quality repair		x								
Complications & side effects		x	x	x	x	x	x	x	x	x
Re-rupture			x	x	x	x	x	x	x	x

*B* baseline, *OR* peri-operative, *w* weeks, *m* months, *y* years, *IKDC* International Knee Documentation Score, *KOOS* Knee Injury and Osteoarthritis Outcome Score, *VAS* Visual Analog Scale, *AP* anteroposterior, *LSI* leg symmetry index

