Ergo, ACL suture repair with dynamic augmentation seems to be a promising technique. However, to date no randomized comparative study has been conducted in which ACL suture repair with dynamic augmentation is compared with the gold surgical standard, ACL reconstruction. This study aims to investigate the hypothesis that suture repair of a ruptured ACL, combined with dynamic augmentation as well as microfracture of the femoral notch, will result in at least equal effectiveness compared with ACL reconstruction using autologous semitendinosus in terms of patient self-reported outcomes (IKDC 2000 subjective scale) 1 year postoperatively.

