### Sample size determination

In order to detect non-inferiority of ACL repair compared to ACL reconstruction surgery in terms of patient self-reported functional outcome measured by the IKDC Subjective score, to achieve a power of 90% and an alpha of 5%, a sample size of 20 patients in each study group is required. According to literature, it seems relevant to consider a standard deviation at nine in both groups [36]. A difference of 11, 5 points in score of IKDC 2000 is suggested as clinically relevant [37]. The margin of equivalence 10 lies within this clinically relevant effect size.

Considering a lost-to-follow-up rate of 20%, it is planned to include 24 patients per randomization group. Thus, in total 48 patients will be included in the study.

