#### Primary study parameter

Differences between IKDC 2000 at baseline and one-year post-operative will be determined for each group, as well as differences between the groups at each follow-up. In case of clinically meaningful differences between groups (> 10 points on the IKDC2000), the non-inferiority hypothesis will be rejected. In case of non-inferiority, superiority analyses will be conducted. For normally distributed data mixed models analyses for repeated measures will be used. In case of non-normally distributed data, the Friedman test for differences within groups, and Mann-Whitney Y test for differences between groups, will be used. A distinction will be made between short term (6 weeks, 3, 6, 9 months and 1 year), mid-term (2 and 5 year) and long-term (10 year) postoperative outcomes.

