To our knowledge, this is the first randomized controlled trial to investigate the functional recovery after ACL suture repair in comparison to ACL reconstruction. This trial has the potential to demonstrate, with a good level of evidence, the effectiveness of ACL suture repair combined with dynamic augmentation as well as microfracture of the femoral notch compared to the gold standard ACL reconstruction using autologous hamstring. As it is not yet clarified what the exact indications for this procedure are and in order to minimize the possible influence of confounding factors on the effectiveness of repair or reconstruction, patients suffering from severe common concomitant injury in ACL rupture, i.e. large meniscal injury needing repair or cartilage injury requiring surgical intervention, were excluded in the current study. Despite the fact that it might limit the generalisability of our findings, it does provide a higher intrinsic validity. If proven at least equally effective, ACL suture repair with dynamic joint bridging stabilisation can be considered as an innovative treatment for ACL ruptures.

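### The stated aim and planned conclusion are that repair is at least equally effective, but success on the test shows only that repair is not worse by more than 10 IKDC points at 1 year

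*Protocol article*

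**What the plan says.** The section Main study parameter/endpoint of the protocol article states: "The primary objective of this non-inferiority study is to determine whether ACL repair will result in at least equal effectiveness compared with ACL reconstruction", measured by the IKDC Subjective score 1 year after surgery. The Methods/design paragraph of the abstract gives the same aim but mentions neither non-inferiority nor a margin. The Background words the hypothesis as repair that "will result in at least equal effectiveness compared with ACL reconstruction using autologous semitendinosus".

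Sample size determination gives the inputs: "A difference of 11, 5 points in score of IKDC 2000 is suggested as clinically relevant"; "it seems relevant to consider a standard deviation at nine in both groups"; and "to achieve a power of 90% and an alpha of 5%, a sample size of 20 patients in each study group is required". On the margin it says: "The margin of equivalence 10 lies within this clinically relevant effect size".

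Primary study parameter, under Statistics, gives the decision rule. If the groups differ by a clinically meaningful amount ("> 10 points on the IKDC2000), the non-inferiority hypothesis will be rejected"). If non-inferiority is shown, superiority is analysed next.

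The Discussion closes with the planned conclusion: "If proven at least equally effective, ACL suture repair with dynamic joint bridging stabilisation can be considered as an innovative treatment for ACL ruptures". That sentence carries no margin, outcome or time point.

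**The concern.** The objective and the test answer different questions. Showing that repair is at least equal means ruling out any deficit, so the lower confidence limit of the difference (repair minus reconstruction) must lie at or above zero. The planned non-inferiority test needs that limit only to lie above -10. Nowhere does the article say that its at-least-equal wording means *not worse by more than 10 points*.

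What is at stake is the published claim. An investigator who follows the article and meets the non-inferiority criterion would, on the Discussion's own terms, conclude that repair is at least equally effective, even if the data were compatible with repair being several points worse. A reader of the abstract alone could not tell the difference.

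**Working it through.** **Inputs.** From Sample size determination: margin 10, SD 9 in each group, power 90%, alpha 5%, 20 evaluable per group, 24 randomised per group, 20% loss. The article does not say whether alpha is one- or two-sided, so one-sided 2.5% and 5% are both shown. It does not state the true difference assumed for the sample size; zero is taken. Evaluable numbers of 19 (24 × 0.8 = 19.2) and 20 (as stated) are both used. Primary study parameter names no confidence limit; a confidence-limit test is assumed.

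**Step 1: the plan's own figure.** For non-inferiority of two means, n per group = 2 × [SD × (z for 1 − alpha + z for power) / margin]².

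- One-sided 2.5%: 2 × [9 × (1.960 + 1.282) / 10]² = 17.02, so 18 (19 with the noncentral t).
- One-sided 5%: 2 × [9 × (1.645 + 1.282) / 10]² = 13.87, so 14 (15 with the noncentral t).

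The stated 20 per group is within 2 of the one-sided 2.5% result. The sample size therefore matches a non-inferiority test with a 10-point margin, and it is not in dispute.

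**Step 2: the largest observed deficit that still passes.** SE = 9 × √(2/n), and the test passes if the observed deficit is below 10 − t × SE, with 2n − 2 degrees of freedom.

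| n per arm | SE | one-sided 2.5% | one-sided 5% |
|---|---|---|---|
| 19 | 2.92 | 10 − 2.028 × 2.92 = 4.1 | 10 − 1.688 × 2.92 = 5.1 |
| 20 | 2.85 | 10 − 5.76 = 4.2 | 10 − 4.80 = 5.2 |

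**Step 3: chance of declaring non-inferiority for a given true deficit.** This is the noncentral t probability with noncentrality (10 − deficit)/SE.

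| True deficit | n = 19: 2.5% / 5% | n = 20: 2.5% / 5% |
|---|---|---|
| 0 | 91% / 96% | 93% / 96% |
| 3 | 64% / 76% | 67% / 78% |
| 5 | 39% / 51% | 40% / 53% |
| 8 | 10% / 17% | 10% / 17% |
| 10 | 2.5% / 5% | 2.5% / 5% |

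**Step 4: what a literal at-least-equal claim would need.** A margin of zero cannot be powered when the true difference is zero. Even small margins are far out of reach: with SD 9, 90% power, one-sided 2.5% and a true difference of zero, a margin of 5 needs 69 per group and a margin of 3 needs 190. The trial is not built to support the wording, and it does not have to be if the wording names the margin.

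**The case against.** The strongest reply is that the phrase is shorthand and the article supplies the qualification. The sentence that sets the objective calls the trial a non-inferiority study, the margin is stated openly beside the cited 11.5 points, and superiority is a separate later step. Every non-inferiority test passes some deficits smaller than its margin, and a margin below the cited clinically relevant difference is ordinary practice. All of that stands: nothing is hidden, and the margin and sample size are not shown to be wrong. It does not rescue the claim, though. The abstract and the Discussion's closing sentence carry neither the margin nor the non-inferiority label, and the separate superiority step confirms that non-inferiority alone does not establish equality or better.

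A reader might infer more: that a clearly poorer repair could be passed off as equal. Under a confidence-limit test the figures do not support this. Observed deficits that pass stop at about 4 to 5 points, under half of 11.5, and a true 10-point deficit passes only 2.5% to 5% of the time. With 20 per arm and SD 9, no result can be both non-inferior and significantly worse, because the two-sided 95% half-width of 5.76 exceeds the largest passing deficit of 5.2. The overlap becomes possible with 24 evaluable per arm at one-sided 5%, or with a smaller SD.

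The stronger reading would follow if the 10-point rule in Primary study parameter were applied to the point estimate, in which case a true 5-point deficit would pass about 96% of the time. The article names no confidence limit there, but it does not say that the point estimate decides either, so this point does not rest on that reading.

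**Conclusion.** The concern holds as a mismatch between claim and test. Success would show that repair is not worse than reconstruction by more than 10 IKDC Subjective points at 1 year, and nothing stronger. With SD 9, 19 to 20 evaluable per arm and a confidence-limit test at one-sided 2.5% or 5%, a repair truly 5 points worse meets the criterion about 39% to 53% of the time, and one truly 3 points worse about 64% to 78%. It is fair to say that a repair *several points worse* could be reported as at least equally effective; *clearly poorer* would go too far. The probabilities depend on the assumed SD, evaluable numbers and sidedness. The mismatch itself depends on none of them, because it follows from any margin greater than zero. It is worth correcting because it changes what the trial may conclude.

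**What to change.** In the abstract (Methods/design), the Background and Main study parameter/endpoint, state the objective as: *IKDC Subjective at 1 year not worse with repair than with reconstruction by more than 10 points*. In the Discussion, make the closing condition: *if non-inferior within 10 IKDC points at 1 year*, reported with the estimated difference and its confidence interval. Reserve any statement that repair is at least equal for a lower confidence limit at or above zero.

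This changes wording only; sample size, margin and endpoint stay as they are. The cost is a less favourable headline claim.

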### Study sample

Patients eligible for enrolment in this study are sportively active patients between 18 and 30 years with a proven primary ACL rupture, confirmed by means of history, physical examination and MRI, for whom an indication for ACL reconstruction surgery exists and who can undergo surgery within 21 days of injury. Exclusion criteria are concomitant large meniscal injury needing repair, cartilage injury requiring surgical intervention or ligamentous lesions of the ipsilateral knee, pre-injury Tegner score below 5, history of knee surgery of the ipsilateral knee, pre-existing significant malalignment of the ipsilateral knee, hypersensitivity to cobalt, chromium or nickel, muscular, neurological or vascular abnormalities, osteoarthritis, use of prednisone or cytostatics, tendency to form excessive scar tissue, pregnancy, osteoporosis or infection.

Patients can withdraw from the study at any time. They will receive appropriate treatment according to standard-care.

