### Intervention

#### ACL suture repair

ACL suture repair will be performed within 21 days after injury. The dynamic intraligamentary stabilisation (DIS) technique will be used (Ligamys, Mathys Medical, Bettlach, Switzerland). The procedure is started with standard arthroscopy to assess all compartments for concomitant injury. When a patient meets one of the exclusion criteria, they will be excluded from the study. Patients will receive further standard care including ACL reconstruction after meeting the Millet criteria. Otherwise, the procedure will be continued and the ACL rupture type will be classified. The tibial attachment of the ACL is identified using an intra-articular guide. A guide wire is overdrilled in the metaphysis and the monoblock is screwed in place. A suture to secure the ACL remnant is inserted through the screw and passed through the ligament and pulled through the femur. The femoral attachment is then marked using a guide from the anteromedial portal. A polyethylene wire will be pulled distally through the femur towards proximal tibia. The wire is stabilized at the femoral position with a cortical suspension button. The polyethylene wire is pulled through the tibia and tightened before final tension is applied. The procedure will be completed by microfracture of the femoral attachment.

Removal of the Ligamys spring will take place in day care, no earlier than after recording of the primary outcome measure 1 year after surgery. The previous anteromedial incision will be used.

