#### ACL reconstruction

ACL reconstruction will be performed when the patient meets the Millett criteria [22], usually approximately 6 weeks after injury. If necessary, additional physiotherapy will be given and patients will be rescheduled for a retest. In that case, the measurements of the retest where the Millet criteria are met will be used as baseline measurement during the study. An all-inside technique (Arthrex, Naples, Florida, USA) will be used. The semitendinosus tendon from the ipsilateral leg will be harvested and quadrupled. A standard arthroscopy will be performed for diagnosis and treatment of concomitant injuries and evaluation of ACL rupture morphology. When a patient meets one of the exclusion criteria, he will be excluded from the study, but the surgical procedure will be continued. ACL rupture will be classified. After removing ACL remnants, the tibial and femoral tunnel will be prepared. The graft will be positioned in the femoral tunnel first and fixed with a cortical suspension button with variable loop length. After, the graft will be placed in the tibial tunnel and fixed with a cortical suspension button, with the knee in 0 degrees of extension while anterior translation of tibia in relation to femur is eliminated. Positioning and tension of the graft will be verified under vision, and if necessary, the graft will be tightened.

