### Randomization

After inclusion, patients will be randomized into an experimental group (repair) or a control group (reconstruction), in blocks with varying sizes (*N* = 2 and *N* = 4) by an independent investigator with PASS (Power Analyses and Sample Size Software; rand.exe version 6.0). The extent of physical activity in daily life poses a potential risk to repair/graft failure. To make sure both groups have an equal risk of failure, patients will be stratified based on physical activity level using the Tegner score (moderate: Tegner 5-7; high: Tegner 8-10) [27, 28].

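### Complications between randomisation and surgery are not scheduled as an outcome, two passages conflict on when recording starts, and the uncovered interval is about 3 weeks or more longer in the reconstruction arm

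*Protocol article*

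**What the plan says.** All of this is in the protocol article.

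- **Schedule.** In Table 1 (Main study parameter/endpoint), the row "Complications & side effects" has no mark at baseline. Its first mark is in the peri-operative column, followed by every visit to 10 years. No column lies between baseline and the operation.
- **Outcome text.** Secondary study parameters, in the part of Methods that defines outcomes, lists reported complications with the IKDC demographic, current-health and history forms as the means of recording baseline characteristics. It later says that failure and other complications will be recorded, with no start date.
- **Order of events.** Under Randomization, allocation follows inclusion. Under Study sample, eligible patients are those "who can undergo surgery within 21 days of injury".
- **Time to surgery.** For repair: "ACL suture repair will be performed within 21 days after injury". For reconstruction: "ACL reconstruction will be performed when the patient meets the Millett criteria [22], usually approximately 6 weeks after injury". The latter section adds: "If necessary, additional physiotherapy will be given and patients will be rescheduled for a retest". It gives no upper limit, and for these patients it makes the passed retest the baseline measurement.
- **Findings at arthroscopy.** Both intervention sections exclude from the study a patient found at arthroscopy to meet an exclusion criterion. Those criteria include large meniscal injury needing repair and cartilage injury needing surgery.
- **Follow-up clock.** Under Study design, follow-up visits are timed from the operation in both arms.

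**The concern.** Patients are randomised before surgery, and one arm then waits longer for it by design. Harm in that wait, such as giving way, new meniscal or cartilage damage, or thrombosis, happens after allocation and belongs to the arm in which it occurs. Table 1 gives it no scheduled entry before the operation. If the outcome text governs instead, it is recorded as a baseline characteristic. For a retested reconstruction patient, that baseline falls after allocation, so harm after randomisation could be described as a starting condition.

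The exclusion rule adds a second route. If new joint damage arises in the wait and meets an exclusion criterion at arthroscopy, the patient leaves the study, and the event may leave the comparison too.

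What is at stake is the comparison of complications by randomised arm. The scheduled timing of the primary endpoint (IKDC Subjective at 1 year after surgery) is not affected. Nor is the sample size, which rests on a margin of 10 points, an SD of 9, 90% power and 5% alpha, none of which involves complications.

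**Working it through.** The plan gives no figure for the length of the safety window, so there is none to reproduce.

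**Inputs**

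- Repair: at most day 21 after injury (ACL suture repair).
- Reconstruction: about day 42, taken from "usually approximately 6 weeks after injury" (ACL reconstruction), and later after a retest.
- Patients per arm: 24 (Sample size determination).
- Day of randomisation after injury, r: not given. Assumed to lie between 0 and 21 and to be alike in both arms, as randomisation would make it on average.

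**Interval from randomisation to surgery**

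Repair: at most 21 − r days. Reconstruction: about 42 − r days.

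| r (days) | Repair, at most | Reconstruction, about | Difference, at least about |
|---|---|---|---|
| 0 | 21 | 42 | 21 |
| 7 | 14 | 35 | 21 |
| 14 | 7 | 28 | 21 |
| 21 | 0 | 21 | 21 |

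The unknown r cancels: (42 − r) − (21 − r) = 21 days. Because 21 days is the maximum for repair, earlier repair widens the difference. So does a retest in the reconstruction arm.

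**Net and gross size**

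- Net: 21 / 7 = 3 weeks per patient; 3 × 24 = 72 patient-weeks.
- Gross, reconstruction: 5 × 24 = 120 patient-weeks at r = 7, and 4 × 24 = 96 at r = 14.
- Gross, repair: at most 2 × 24 = 48 at r = 7, and 1 × 24 = 24 at r = 14.
- Check: 120 − 48 = 72 and 96 − 24 = 72.

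**Scale**

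- First postoperative year for one arm: 24 × 52 = 1,248 patient-weeks; 72 / 1,248 = 5.8%.
- Ten years: 24 × 520 = 12,480 patient-weeks; 72 / 12,480 = 0.6%.
- One patient with an event: 1 / 24 = 4.2 percentage points in that arm. This shows only how coarse a count in 24 patients is. The article gives no event rate for the wait, so no expected number of missed events can be derived.

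**The two passages side by side**

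- If Table 1 governs, complications have no scheduled entry at baseline. The first entry is peri-operative, and nothing says whether it looks back over the wait.
- If the outcome text governs, complications reported at baseline describe the patient's starting state.
- Under either reading, an event between randomisation and surgery is not assigned to the outcomes.

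**The case against.** The strongest case on the other side is that the schedule shows when data are taken, not which events qualify. The peri-operative mark comes after the wait and is nowhere limited to intraoperative events. IKDC current health and history are marked both at baseline and peri-operatively, and concomitant injury is recorded at surgery. Complications do not appear in the list of secondary analyses under Statistics, and the article describes its aim as a comparison of two operations with postoperative outcomes. It also condenses a fuller protocol, which may define when adverse-event reporting starts.

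Much of this stands, and it rules out several stronger readings that a reader might infer:

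- **That complications are collected only from surgery and harm in the wait is never counted.** The baseline mention in the outcome text contradicts this, and the general statement on recording complications has no start date.
- **That the arms have unequal safety windows.** The scheduled window, from the operation to 10 years after it, is the same in both. Only the interval before surgery differs.
- **That a patient who never has surgery has no safety record at all.** That is an inference from the schedule. Study design provides for contact after missed visits, and the full protocol may say more.
- **That the re-rupture row starting at 6 weeks shows the same gap.** A repair or graft cannot re-rupture before it exists.
- **That the uncovered time is 96 to 120 patient-weeks and falls almost wholly on one arm.** That is the gross figure for reconstruction at r = 7 to 14. Repair has up to 24 to 48 of its own.
- **That the plan flatters reconstruction.** This holds only if events occur in the wait and are then missed.

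The objection does not remove the conflict. Table 1 and the outcome text are both printed in this article and disagree on whether complications are taken at baseline, so the point does not depend on what a short article leaves out. The forms that might pick up an event incidentally do not make it an outcome of the randomised arm.

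**Conclusion.** The point holds in a limited form. The article contradicts itself on when complication recording starts, and neither passage counts harm between randomisation and surgery as an outcome. The uncovered interval is longer in the reconstruction arm by about 3 weeks or more per patient, net about 72 patient-weeks over 24 patients.

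This rests on reconstruction at the usual 6 weeks or so, repair by day 21, similar randomisation days in the two arms, and 24 patients per arm. It does not depend on which day randomisation falls. If events occur in the wait, a complication comparison by arm would miss more of them under reconstruction. A patient excluded at arthroscopy for new damage would be one concrete case. How many events are involved cannot be estimated from the article. The time is small against the whole follow-up, but the imbalance is built into the design and cheap to remove.

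**What to change.** - **Reconcile the passages.** Make Table 1 and the outcome text on secondary study parameters agree, and state that complication recording starts at randomisation in both arms.
- **Add one entry.** Add a randomisation-to-surgery entry to the complications row, completed at the existing peri-operative visit. For patients who are never operated on, complete it by contact.
- **Report by randomised arm from randomisation.** Include patients excluded at arthroscopy. Keep the postoperative-only count as a secondary table.
- **Annotate arthroscopic findings.** Note beside each one whether it was visible on the baseline MRI. Treat this as description only, since a lesion missed on MRI is not proof of a new event.

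The cost is a wording change and one extra case report form entry. Visits, treatment and sample size stay as they are. The control arm's complication count may turn out slightly higher.
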